## Abstract

**Background:**

Recent estimates indicating that approximately 10% of fathers experience Paternal Perinatal Depression (PPND) and the increasing evidence of the impact of PPND on child development suggest that identifying and assisting distressed fathers is justified on public health grounds. However, addressing new fathers’ mental health needs requires overcoming men’s infrequent contact with perinatal health services and their reluctance to seek help. Text-based interventions delivering information and support have the potential to reach such groups in order to reduce the impact of paternal perinatal distress and to improve the wellbeing of their children. While programs utilising mobile phone technology have been developed for mothers, fathers have not been targeted. Since text messages can be delivered to individual mobile phones to be accessed at a time that is convenient, it may provide a novel channel for engaging with “hard-to-reach” fathers in a critical period of their parenting.

**Objective:**

The study will test the efficacy of SMS4dads, a text messaging program designed specifically for fathers including embedded links to online information and regular invitations (Mood Tracker) to monitor their mood, in order to reduce self-reported depression, anxiety and stress over the perinatal period.

**Methods:**

A total of 800 fathers-to-be or new fathers from within Australia will be recruited via the SMS4dads website and randomized to the intervention or control arm. The intervention arm will receive 14 texts per month addressing fathers’ physical and mental health, their relationship with their child, and coparenting with their partner. The control, SMS4health, delivers generic health promotion messages twice per month. Messages are timed according to the babies’ expected or actual date of birth and fathers can enroll from 16 weeks into the pregnancy until their infant is 12 weeks of age. Participants complete questionnaires assessing depression, anxiety, stress, and alcohol at baseline and 24 weeks postenrolment. Measures of coparenting and parenting confidence are also completed at baseline and 24 weeks for postbirth enrolments.

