### Inclusion Criteria

Participants will be included in the trial if they indicate having a partner who is more than 16 weeks pregnant or their infant is less than 12 weeks of age, have a mobile phone capable of receiving text messages, and they can read and understand English. There is no cost involved in receiving the text messages but access to the internet is required to respond to the Mood Tracker texts and to access the links provided to websites in the messages.

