### Screening and Baseline

Expecting and new fathers will register for participation through the project website where an information statement and other materials about the project are readily available [39]. Fathers wishing to enrol can click on the “Join Up” tab located on the front page of the SMS4dads website, which will take them to the registration pages. The first registration pages assess eligibility and information for messaging purposes including their infant’s expected or actual date of birth, full name, email address, and phone number. For demographic purposes, they will be asked for their age, postal address, Indigenous status, and a question about their socioeconomic position [37]. When completing consent questions fathers will be asked to confirm that they have read the information statement and that they have no further questions about the project. They will also be asked if they would like to be informed of study outcomes, if they would be willing to participate in phone interviews about their experience of participation, and whether they would be prepared to pass an information package onto their partner. When fathers have answered these questions they will be asked to respond to four questionnaires (53 items) detailed in the following section on study measures. All questions mandate a response but fathers can report that they have no email address and that they do not wish to supply data about their socioeconomic position.

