### Follow-Up Assessments

Fathers are also asked to repeat the questionnaires 24 weeks after receiving their first message.

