### Program Content, Tone, and Design

The program content includes an established corpus of relationship-focused messages developed for a related feasibility study using an iterative consultation process with parents, academics, and practitioners (N=46) [41,42]. Messages aim to provide new fathers with information, support them in caring for their own physical and mental health, nurturing strong relationships with their child, and developing strong parenting partnerships with their partner. Messages are timed according the babies expected or actual date of birth and thereby designed to address issues that are likely to be occurring for the father when the information arrives. Messages, including links, are limited to 160 characters and designed to engage with fathers through humor, by use of the baby’s voice, and through an encouraging, nonjudgemental tone. Approximately one third of messages (n=98) contain links to online sources of information directly related to the message content [41].

A father participating in the full 77-week program will receive 294 messages. These are usually delivered on a 4-week cycle (5 messages in week 1, 4 in week 2, 3 in week 3, and 3 in week 4) totalling 15 messages. Some messages address particular issues such as alcohol consumption (n=25) and others link to the Mood Tracker application (n=30). Mood Tracker messages ask fathers to respond to questions about their mood on a 5-point scale. Fathers indicating high levels of distress on Mood Tracker will be automatically linked to appropriate websites and offered the opportunity to be contacted by a phone counselling service experienced in paternal perinatal support.

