### Data Analyses

Given that there are multiple measures of the primary outcome, ie, DASS-21 scores at baseline and 24 weeks, we will use a linear mixed–model to analyse the results. This model will handle repeated measures as well as missing data; the model will include terms for group, time, and group x time interaction, which will allow us to see if the effect is more marked in one group versus another at particular time points. Secondary outcomes such as parenting, coparenting, and alcohol scales will be analysed using similar models.

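### The primary model has no term for perinatal stage at enrolment, although the 24-week outcome falls anywhere from about the due date to 36 weeks postpartum and the birth date is collected at registration

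*Protocol article*

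**What the plan says.** **Entry.** The abstract (Methods) says that "fathers can enroll from 16 weeks into the pregnancy until their infant is 12 weeks of age". The Inclusion Criteria agree in substance and accept fathers "having a partner who is more than 16 weeks pregnant or their infant is less than 12 weeks of age".

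**Outcome timing.** The abstract places the questionnaires "at baseline and 24 weeks postenrolment". The Follow-Up Assessments section asks fathers to "repeat the questionnaires 24 weeks after receiving their first message". Either way the clock starts at entry to the trial and not at the birth.

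**Model.** Under Data Analyses, for DASS-21 at baseline and 24 weeks, "the model will include terms for group, time, and group x time interaction". Enrolment stage is not among the listed terms. The Sample Size section mentions adjustment for baseline values only. The Randomization section describes permuted blocks of 4 or 6 and states no stratification factor.

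**Available data.** Under Screening and Baseline, the first registration pages collect "information for messaging purposes including their infant’s expected or actual date of birth". Stage at enrolment can be derived from this for each father before he is allocated.

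**The concern.** The time term has two levels, entry and 24 weeks later, and it describes one average change over that interval. The interval covers different events for different fathers. A man who enrols during the pregnancy usually goes through the birth between his two assessments. A man who enrols afterwards has the birth behind him at both. The baseline score is also taken at different perinatal stages, so the time term mixes time since enrolment with time since birth.

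If DASS-21 changes differently over 24 weeks according to stage, the stated model leaves that variation in the residual. Because no stratification by stage is stated, a chance difference between arms in the mix of antenatal and postnatal enrolees would also go uncorrected. At stake are the precision of the treatment estimate and its robustness to that imbalance. The validity of the trial is not in question.

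**Working it through.** **1. Timing of the outcome.** Inputs are the entry window (abstract, Inclusion Criteria) and the 24-week interval. Term is taken as 40 weeks, and enrolment and first message are treated as the same date.

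- Earliest: 16 + 24 = 40 weeks' gestation, about 0 weeks postpartum. Some of the earliest enrolees may be assessed just before the birth.
- Latest: 12 + 24 = 36 weeks postpartum.
- Width of the window: (40 − 16) + 12 = 36 weeks.

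**2. The plan's own sample size.** Inputs (Sample Size) are an effect of 0.5 SD among distressed fathers, 80% power, 5% significance, taken as two-sided, and 1:1 allocation. The noncentral t distribution with noncentrality 0.5 × √(64/2) = 2.83 and 126 degrees of freedom gives 80.1% power at 64 per arm. Then 64/0.20 = 320 per arm, 640 in total, and 640/0.80 = 800. The stated figures reproduce.

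**3. Precision gained by adjusting for stage.** Let R² be the share of outcome variance that stage explains. The article gives no value, so a range is assumed. Adjustment multiplies the residual SD by √(1 − R²), so the standardised effect becomes 0.5/√(1 − R²). Required n is 64 × (1 − R²), rounded up.

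| Assumed R² | Power at 64 per arm | Required n per arm |
|---|---|---|
| 0 | 80.1% | 64 |
| 0.01 | 80.5% | 64 |
| 0.02 | 80.9% | 63 |
| 0.05 | 82.1% | 61 |
| 0.10 | 84.1% | 58 |

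If the 0.5 SD is instead read as relative to the within-stage SD, the unadjusted analysis has 79.4% power at R² = 0.02 and 78.1% at R² = 0.05. The difference is again about 1 to 2 points.

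To see what an R² of this order would require, suppose that enrolment is uniform over the window, so that 24/36 = two-thirds are antenatal, and that the two stages differ by d SD. The variance due to stage is d² × (2/3) × (1/3), which is 0.02 at d = 0.3 and 0.056 at d = 0.5. Both the share and the values of d are assumptions.

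**4. Chance imbalance.** With the same two-thirds share and 64 per arm, the SD of the between-arm difference in antenatal share is √(2 × (2/9)/64) = 0.083, about 8 percentage points. One SD of imbalance shifts the treatment estimate by 0.083 × 0.3 = 0.025 SD to 0.083 × 0.5 = 0.042 SD. The standard error of the estimate is √(2/64) = 0.18 SD. With 320 per arm the imbalance SD is √(2 × (2/9)/320) = 0.037.

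**5. Can the effect be compared between stages?** In 128 distressed fathers, the standard error of a stage-by-treatment interaction is √(4/n₁ + 4/n₂), where n₁ and n₂ are the numbers in each stage. Power for a 0.5 SD difference in effect is Φ(0.5/SE − 1.96).

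- Even split (64 and 64): SE = √0.125 = 0.354, power about 29%.
- Two to one (85.3 and 42.7): SE = √0.1406 = 0.375, power about 27%.

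**6. Which stage term matters.** A stage difference of equal size at baseline and at 24 weeks largely cancels from the group-by-time contrast. Only a difference between stages in the change over time remains, so a main effect of stage alone would do little and stage by time is needed.

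**The case against.** The strongest reply is that the article is condensed. It says what the model will include and does not rule out further covariates, and a separate analysis plan could add stage. That stands as a limit on the point: the listed model can be improved at almost no cost, but omitting the covariate is not an error. If the analysis plan already has the term, the point is met.

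Second, the gain is small and rests on an assumed stage effect that could be zero. This also stands. Ordinary chance imbalance is already reflected in the standard error, and the type I error is unaffected.

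Third, a reader might infer that the spread of outcome times biases the treatment effect. The documents do not support that. Stage is fixed before allocation, so it is independent of arm in expectation.

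Fourth, a reader might infer that the pooled result cannot be interpreted. That does not follow either. The trial sets out to enrol both expectant and new fathers and its objective covers the perinatal period, so an effect averaged over stage is what it was designed to estimate. Adding stage and stage by time would not change what that average means.

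**Conclusion.** The point holds as a low-cost improvement to the stated model. The outcome window of about 0 to 36 weeks postpartum, the absence of stage from the listed terms and the collection of the birth date all follow from the text. The cost of leaving stage out is roughly 0 to 2 percentage points of power at 64 per arm if stage explains 0 to 5% of variance. On the assumed stage differences of 0.3 to 0.5 SD, a typical chance imbalance shifts the estimate by 0.025 to 0.042 SD against a standard error of 0.18. These sizes rest on assumed stage effects and an assumed two-thirds antenatal share, for which the article gives no figures.

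A reader might also set the 24-week endpoint against the statement "A father participating in the full 77-week program will receive 294 messages" and infer that the trial misdescribes what it tests, since 24/4 × 15 = 90 messages is 31% of 294. This is not supported: the Hypotheses section fixes the comparison at 24 weeks after baseline, and how many messages have been sent has no bearing on whether stage belongs in the model.

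**What to change.** Pre-specify in the primary model a covariate for enrolment stage, together with its interaction with time. Stage can be weeks from the expected or actual birth at enrolment or, at the least, antenatal versus postnatal. Derive it from the date given at registration so that it is a pre-randomisation quantity. Record the choice before outcome data are analysed. The Results section describes follow-up as still in progress, so on the article's own timetable this was possible.

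Treatment effects by stage may be reported with confidence intervals, labelled descriptive, and not used to claim that the programme works at one stage and not at another.

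The cost is a change of wording in the analysis section and one or two degrees of freedom. No new data, participants or changes to conduct are needed.

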**Results:**

Participant were recruited between October 2016 and September 2017. Follow-up data collection has commenced and will be completed in March 2018 with results expected in June 2018.

**Conclusions:**

This study’s findings will assess the efficacy of a novel text-based program specifically targeting fathers in the perinatal period to improve their depression, anxiety and distress symptoms, coparenting quality, and parenting self-confidence.

**Trial Registration:**

Australian New Zealand Clinical Trials Registry ACTRN12616000261415; https://www.anzctr.org.au/ Trial/Registration/TrialReview.aspx?id=370085 (Archived by WebCite at http://www.webcitation.org/6wav55wII).

## Introduction

The period surrounding childbirth represents a vulnerable time for families where both women and men may be at increased risk of mental health disorders. However, while maternal perinatal screening and treatment protocols have been introduced within Australia, Paternal Perinatal Depression (PPND) has been largely overlooked [1]. Recent estimates indicating that 9% to 10% of fathers experience PPND [2,3] and the increasing evidence of the impact of PPND on child development [4,5] suggest that identifying and assisting distressed fathers is justified on public health grounds. In similar fashion, high levels of paternal anxiety and stress have also been found to be harmful to children’s development [6-8]. However, addressing new fathers’ mental health needs requires overcoming men’s infrequent contact with perinatal health services and their reluctance to seek help [9,10].

While anxiety, stress and depression are recognized as related negative emotional states, paternal depression has figured most prominently in the published research on fathers’ mental health in the perinatal period. PPND can impair the fathers’ relationship with his infant and reduce his ability to effectively coparent. Observational studies of depressed fathers have found decreased levels of warmth, sensitivity, synchrony engagement, and positive involvement and increased levels of criticism, hostility, harshness, intrusiveness, withdrawal, and control [11]. For example, fathers of one year olds who had experienced a major depressive episode in the previous year were only half as likely to read to their infants but four times more likely to spank them [12].

The detrimental impact of PPND on fathers' mental wellbeing and on infant development is well documented. Preschoolers whose fathers reported symptoms of depression in the first year had twice the risk of behavioral and emotional problems compared to children of nondepressed fathers [13]. When the children were assessed at 7 years of age, those whose fathers had been depressed following their birth were almost twice as likely to have a psychiatric disorder compared to those of nondepressed fathers [4]. In both studies, findings were consistent after adjusting for maternal depression and paternal educational level. In addition, analysis of an Australian cohort found highly elevated behavior problems in preschool children whose fathers had shown depressive symptoms in their first year [5].

PPND, expressed through hostility and negative comments, is also likely to impact on the relationship between the parents, especially when combined with alcohol dependence [14,15]. Couple conflict and lack of partner support has been linked to maternal postnatal depression [16,17], and marital conflict may help to explain the relationship between postnatal depression in either mothers' or fathers' and child outcomes [18,19].

Given the deleterious effects of PPND on a father's own health, his parenting and coparenting relationship, and the possible ongoing impairment of his child's development, the need to identify and treat or support distressed fathers is clear. Moreover, health service costs of PPND in Australia, using 2012 figures, have been estimated at $17.97 million with an added cost of $223.75 million due to lost productivity [20]. While calls for fathers to be assessed for mood disorders and offered information, support, and counselling during the perinatal period are common, the service response has been absent [21].

Addressing PPND will require overcoming several barriers. Work demands, for example, prevent most fathers participating in perinatal clinic visits with their partner [9]. Those fathers attending antenatal preparation classes or the birth may feel ignored by professionals and feel that they have few opportunities to raise their concerns [22,23]. As well, fathers may have little understanding of perinatal depression in general and may not easily recognize their own symptoms of depression [24,25]. Attempts to engage fathers in early intervention programs have had little success and fathers are badged as “hard to reach” [26,27].

Mobile phone technology may be feasible in identifying distressed fathers and offering support as ownership among Australian adults is high (94%) [28]. Fathers regularly use the Internet to source parenting information [29,30]; however, linking fathers to Web-based parenting resources remains problematic. The low recruitment and engagement of fathers found in face-to-face parenting programs [28] appears to be replicated in online parenting programs [31,32].

Text messaging has been shown to influence health-related knowledge and beliefs among mothers. Text4baby, a United States–based program sending short message service messages to mothers through the perinatal period, has found that 75% of users reported text messaging had given them important medical information. A randomized controlled trial involving 90 Text4baby users found that text messaging was associated with positive alterations in targeted health beliefs [33]. Health behaviors relating to smoking, weight loss, physical activity and the management of diabetes have also shown improvement in response to text messaging [34,35]. Text messaging could therefore provide a novel avenue for delivering support and parenting-related information to fathers during their transition to fatherhood.

While texts, which are delivered at no cost to participants, are able to convey information relevant to a father’s role during pregnancy and postbirth, they have limited capacity to engage fathers in help seeking. Self-monitoring to increase participants’ awareness of their mood has been incorporated into web and mobile phone programs targeting depression [36,37] with embedded links to websites for further information, education, or support. Providing links within messages to websites that are relevant to fathers' concerns and including interactive text messages inviting mood self-monitoring (Mood Tracking) may encourage fathers to seek out assistance for parenting difficulties and for personal distress.

Text-based interventions delivering information and support have the potential to reduce the impact of perinatal distress in parents and improve the wellbeing of their children. While programs utilising mobile phone technology have been developed for mothers’ mental health [38] fathers have not been targeted. The study proposed here will test the efficacy of a program incorporating brief text messages designed specifically for fathers including embedded links to online information and support and regular invitations (Mood Tracker) to monitor their mood (see Multimedia Appendices 1, 2, and 3). Since text messaging is relatively inexpensive and can be accessed across rural and urban areas at a time that is convenient, it may provide a novel channel for reaching “hard-to-reach” fathers in a critical period of their parenting. SMS4dads may offer a low-cost model for improving the wellbeing of families through supporting the male partner in the parenting team.

The aim is to conduct the first randomized controlled trial of a text-based intervention, SMS4dads, which targets fathers’ mental health during the perinatal period. The efficacy of the SMS4dads program in reducing depression, anxiety, and stress symptoms among new fathers will be assessed by comparing intervention outcomes with those of a sham program, SMS4health, offering generic health promotion messages. Secondary aims are to assess the effect of SMS4dads on the fathers’ coparenting, parenting self-confidence, and use of alcohol.

### Hypotheses

It is predicted that fathers receiving the SMS4dads program will show lower levels of depression, anxiety, and distress at 24 weeks postbaseline than fathers receiving the SMS4health program. In addition, fathers’ coparenting and parenting self-confidence are predicted to be greater and use of alcohol to be less among those receiving SMS4dads than among those receiving SMS4health.

## Methods

This randomized controlled trial is designed to assess the efficacy of a text-based intervention targeting mental health in new fathers. Participating fathers will be randomly allocated to receive either the SMS4dads or SMS4health. A summary of participant flow though the trial is provided in Figure 1. This study received ethics approval from The University of Newcastle Human Research Ethics Committee on June 16 2016, approval number H-2016-0055.

